## SUMMARY

**Rationale:** When treating older patients with dizziness in primary care, the current diagnosis oriented approach is insufficient. Often, it is not possible to diagnose an underlying disease and even if a disease is diagnosed, therapeutic options are often limited. In this study a prognosis oriented approach for dizziness in older people in primary care will be investigated.

**Objectives:** In this study we want to validate a risk score for chronic dizziness with persistent impairment in older dizzy patients in general practice. Furthermore, we want to investigate the effectiveness of a risk factor-guided, i.e. a prognosis-oriented, intervention for dizzy older patients with a high risk of persistent impairment.

**Study design:** The study protocol consists of two parts. Firstly, we will perform a validation study to externally validate a 7-item risk score for chronic dizziness with persistent impairment. Secondly, we will perform an intervention study, using a cluster controlled clinical trial. In the intervention study we will compare the effectiveness of a targeted intervention for dizzy older patients with a high risk of persistent impairment with usual care during one year of follow-up.

**Study population:** 375 patients aged 65 years or older who consult their general practitioner (GP) for a new episode of dizziness existing for at least one month.

**Intervention:** In older patients with a high risk of persistent impairment because of dizziness we will compare a risk factor-guided intervention consisting of one, two, or three of the following interventions: (1) medication adjustment in case of the usage of  $\geq 3$  Fall Risk Increasing Drugs (FRIDs), (2) stepped care in case of anxiety/depression, and (3) exercise therapy in case of impaired functional mobility. All three interventions are evidence based and usual care for the above-mentioned risk factors.

**Main study parameters/endpoints:** The primary clinical outcome is dizziness related impairment at follow-up, which will be assessed using the Dizziness Handicap Inventory (DHI). Secondary outcomes are quality of life (EQ-5D-5L), difference in 'Fall Risk Increasing Drug' count, anxiety/depression, dizziness frequency, fall frequency, health care utilization.

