### Secondary Objectives:

1. To investigate if a targeted intervention in older dizzy patients in general practice will reduce dizziness frequency and fall incidence.
2. To assess if health care utilization of older dizzy patients receiving a targeted intervention will decrease compared to older dizzy patients receiving usual care.
3. To investigate if our targeted intervention is cost-effective.
4. To investigate if older dizzy patients with significant dizziness-related impairment have more often an anxiety- or depressive disorder than non-impaired older dizzy patients in general practice.
5. To investigate the course of anxiety and depression in older dizzy patients in general practice during one year of follow-up.

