### 3. STUDY DESIGN

Both the validation study and the intervention study will be combined in a three-arm design with a follow-up of 1 year. Allocation to the intervention and control condition of the intervention study will be carried out at practice level (cluster randomisation) to avoid contamination.

The figure below represents the flowchart of the study with an overview of the group classification and randomisation. The given percentages are estimates based on secondary analysis of DIEP data.

[figure not shown]

The figure shows that all dizzy older patients will be assigned to group A, B, or C. Assignment to one of the three groups is based on the presence of significant dizziness related impairment at baseline and having a high risk of chronic dizziness with persistent impairment or not. Dizziness related impairment will be assessed with the Dizziness

Handicap Inventory (DHI). A DHI score of  $\geq 30$  correlates with current significant impairment because of dizziness. A dizzy older patient will be labelled as high risk for chronic dizziness with persistent impairment in case of a DHI  $\geq 30$  and the presence of one, two or three of the following risk factors: usage of three or more Fall Risk Increasing Drugs (FRIDs), anxiety and/or depression, and impaired functional mobility.

Summarizing there are three groups: dizzy older patients with significant impairment but at low risk of chronic dizziness with persistent impairment (group A, n=125) and dizzy older people with significant impairment and at high risk of chronic dizziness with persistent impairment (group B and C, n=125 each). Dizzy older people with significant impairment and a high risk of chronic dizziness will be randomised to group B or C (randomisation will take place at practice level). The validation study consists a low risk usual care group (group A) and a high risk usual care group (group B). The intervention study consists of impaired dizzy patients with a 'high risk' that will receive usual care (group B) or an intervention (group C).

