### 4.2 Inclusion criteria

In order to be eligible to participate in this study, a subject must meet all of the following criteria:

- being 65 years or older
- consulted a general practitioner for a new episode of dizziness, defined as recurrent dizziness for at least one month, including a giddy or rotational sensation, loss of balance, faint feeling, light-headedness, instability, or tendency to fall
- current dizziness-related impairment (DHI  $\geq$  30)
- ability to speak, read and write Dutch

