#### Recruitment of patients

Patients will be recruited via two routes: through identification of patients by the GPs and via searches in the electronic medical databases (EMD) of the GPs. We will use the strategy of identification of patients by the GP since this has been proven to be successful in the DIEP study. In addition to this we will ask the GP's to do a search in their EMDs every three months to make sure we will not miss eligible patients.

Identification of patients by the GPs will take place during consultation hours. If a GP sees an eligible patient for this study, the GP will inform the patient about the presence of the study and will ask for the patients' permission to be approached by the researcher. If the patient has given his/her permission, the GP will register the obtained permission in the EMD and inform the researcher (by fax or e-mail) about the patient's name and address. The researcher will then send the patient an invitation letter.

Secondly, the GP will be asked to execute a search in his/her EMD every three months. The GP will exclude all identified dizzy patients that fulfil the exclusion criteria. The researcher will then check which patients have not yet been invited to participate in the

study. Patients identified through searches in the EMD will receive an invitation letter on behalf of their GP.

Additionally to the invitation letter, all patients will receive a brochure with study information, a contact form and the DHI-S. Patients will be asked to fill out the DHI-S if they want to participate in the study. All patients with a DHI-S of  $\geq 12$  will receive a phone call of the researcher to set an appointment for baseline assessment at the patients home. Patients with a DHI-S score of  $< 12$  are not eligible to participate in the study.

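### Secondary objective 4 needs non-impaired dizzy patients, but 0 of the 375 enrolled are non-impaired at baseline and no outside comparator is described

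*Protocol*

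**What the plan says.** The fourth secondary objective in section 2 compares two kinds of older dizzy patient. It asks whether those with significant dizziness-related impairment "have more often an anxiety- or depressive disorder than non-impaired older dizzy patients in general practice". It names no time point.

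Four other places govern who can be in the data:

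- Section 4.2 states that "a subject must meet all of the following criteria", and one of these is "current dizziness-related impairment", set at a DHI of 30 or more.
- Section 11.2 (Recruitment of patients) screens by post with the DHI-S. Patients scoring 12 or more are called for a baseline appointment; those below 12 "are not eligible to participate in the study".
- Section 3 defines the first group as "dizzy older patients with significant impairment but at low risk of chronic dizziness with persistent impairment (group A, n=125"). Its description of the other two, B and C, also requires impairment; what sets them apart from A is their high-risk label. Each of these has 125 patients as well.
- The Summary gives the whole study population as "375 patients aged 65 years or older who consult their general practitioner (GP) for a new episode of dizziness" that has lasted at least a month.

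Section 3 also says that assignment to A, B or C rests partly on whether significant impairment is present at baseline, although all three groups have it.

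The table in section 8.3 schedules the DHI, PHQ-9, GAD-7 and PHQ-PD at baseline, 6 and 12 months for validation and intervention study participants (also at 3 months in the intervention study). Sections 10.1 and 10.2 describe no analysis of impaired against non-impaired patients.

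**The concern.** An objective that contrasts two populations needs data from both. Here the rules that define the study population remove one of them, so the conflict lies between two parts of the protocol. An analysis plan can choose a model, but it cannot supply patients whom eligibility keeps out.

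At stake is what the trial can claim. If the text stays, the objective may simply go unreported, or someone at the analysis stage may take the nearest available contrast. Low-risk against high-risk patients is an obvious candidate, and it would give a positive answer whatever the truth, because anxiety or depression is one of the factors that make a patient high risk.

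**Working it through.** **1. The planned total.** Inputs: the three group sizes in section 3. 125 + 125 + 125 = 375, which reproduces the Summary's figure. No patients are left over for a fourth group.

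**2. Non-impaired patients at baseline.** Groups A, B and C are each defined as impaired, and section 4.2 makes a DHI of 30 or more compulsory. Impaired: 375. Non-impaired: 375 − 375 = 0. The prevalence of anxiety or depression in the comparison group is then 0/0, so neither a difference nor a power can be computed. The protocol gives no sample size for this objective to check.

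**3. Other planned sources of comparators.** The anxiety and depression instruments are scheduled only for study participants (section 8.3 table). Sections 10 to 10.2 mention no external cohort or reference data for this question.

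**4. Group A as a substitute.** Section 3 labels a patient high risk if the DHI is at least 30 and at least one of three factors is present: three or more fall-risk-increasing drugs, anxiety and/or depression, or impaired functional mobility. An impaired patient who is low risk therefore has none of the three.

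- Anxiety/depression in A at baseline: 0 of 125, by definition.
- Section 5.1 expects 48% of group C to qualify for stepped care, the intervention for anxiety/depression. Assuming the same share in B, B and C together would have 0.48 × 250 = 120 of 250.
- A against B/C would then show 0% against 48%. The 0% is fixed by the group definition, and both sides of the contrast are impaired.

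**5. What follow-up can offer.** Section 4.4 (validation study) expects 60% of patients with a DHI of 30 or more at baseline still to be at 30 or more at 6 months, and applies this to the 250 patients in A and B.

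| Usual-care patients (A + B) at 6 months | DHI 30 or more | DHI below 30 |
|---|---|---|
| No loss (250) | 0.6 × 250 = 150 | 0.4 × 250 = 100 |
| 20% loss assumed (0.8 × 250 = 200) | 0.6 × 200 = 120 | 0.4 × 200 = 80 |

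The 150 is the protocol's own figure. The 20% loss is stated in section 4.4 for the intervention study only; applying it to A + B, and treating it as unrelated to impairment, are assumptions. No corresponding percentage is given for 12 months.

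**The case against.** **The objective does not say baseline.** This is the strongest point. Section 8.1.1 dichotomises all DHI scores for the validation study, and section 8.3 repeats the DHI and the anxiety and depression measures at 6 and 12 months. Patients below 30 with concurrent measures will therefore exist. A reader might infer from the zero count that the trial can say nothing about impairment and anxiety or depression. The documents do not support that: the zero holds at baseline, and step 5 shows usable numbers later. What remains is that patients who improved out of an impaired cohort are not the non-impaired dizzy patients of general practice whom the objective names. Some may no longer be dizzy at all.

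**Nobody proposed comparing A with B/C.** True. A reader might infer that this circular contrast is the only one left, or is planned. Neither is so: the protocol does not mention it for this objective, and the follow-up contrast is another possibility. The warning in step 4 concerns a likely misuse.

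**Some non-impaired patients may have data.** A patient with a DHI-S of 12 or more could score below 30 on the full DHI, having consented and completed the baseline questionnaires. A reader might infer from the 0 of 375 that no such records can exist. The documents do not rule them out. But section 4.2 excludes these patients, they belong to no group, and no use of their data is described. They would also be a selected set, since all passed an impairment screen.

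**The flowchart is not visible.** It might contain a non-impaired branch. The section 3 text that summarises it, the inclusion criteria and the Summary's account of all 375 patients make an enrolled non-impaired group very unlikely.

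**This is a secondary objective whose analysis may sit in an SAP.** That limits the weight of the point but does not remove the conflict between objective and eligibility.

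**Conclusion.** The point holds in this form: as worded, secondary objective 4 cannot be answered at baseline, because 0 of 375 enrolled patients are non-impaired and no comparator from outside the study is described. This rests on the inclusion criterion and group definitions being applied as written. Group A is not a valid substitute.

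It does not follow that the trial has nothing to say on the topic. Related questions can be answered from scheduled data, with about 150 against 100 usual-care patients at 6 months, or 120 against 80 if the 20% loss is assumed to apply.

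The text should be corrected, but the consequence is limited. Neither primary objective, nor the randomisation, nor the sample size depends on it.

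**What to change.** Delete secondary objective 4, or replace it with a question the scheduled data can answer:

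- **(a)** the association of baseline DHI, within the range 30 to 100, with PHQ-9, GAD-7 and PHQ-PD among impaired patients; or
- **(b)** anxiety and depression at 6 and 12 months in usual-care patients (A + B) with persistent impairment, against those whose DHI has fallen below 30.

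Whichever is chosen:

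- Say that it is a different question from impaired against non-impaired patients in general practice.
- Account for the fixed quotas of 125 per group, for example by stratifying or weighting by group, because anxiety/depression helps to determine membership. For (a), weighting is likely to serve better: group A has no baseline disorder by definition, so stratifying leaves little to compare there. Weighting needs the ratio of low-risk to high-risk patients among those eligible, so that ratio should be recorded at recruitment.
- State that A against B/C will not be used for this question.
- Reconcile the section 3 statement that assignment depends on the presence of impairment with section 4.2, under which every participant is impaired.

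The cost is a few sentences in sections 2 and 3, a short analysis note and a recruitment count, with no new patient measurements. The downside is that the trial no longer claims the contrast now named in objective 4. Keeping that contrast would require a non-impaired group with its own anxiety and depression measurements, which is a larger change.

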### 3. STUDY DESIGN

Both the validation study and the intervention study will be combined in a three-arm design with a follow-up of 1 year. Allocation to the intervention and control condition of the intervention study will be carried out at practice level (cluster randomisation) to avoid contamination.

The figure below represents the flowchart of the study with an overview of the group classification and randomisation. The given percentages are estimates based on secondary analysis of DIEP data.

[figure not shown]

The figure shows that all dizzy older patients will be assigned to group A, B, or C. Assignment to one of the three groups is based on the presence of significant dizziness related impairment at baseline and having a high risk of chronic dizziness with persistent impairment or not. Dizziness related impairment will be assessed with the Dizziness

Handicap Inventory (DHI). A DHI score of  $\geq 30$  correlates with current significant impairment because of dizziness. A dizzy older patient will be labelled as high risk for chronic dizziness with persistent impairment in case of a DHI  $\geq 30$  and the presence of one, two or three of the following risk factors: usage of three or more Fall Risk Increasing Drugs (FRIDs), anxiety and/or depression, and impaired functional mobility.

Summarizing there are three groups: dizzy older patients with significant impairment but at low risk of chronic dizziness with persistent impairment (group A, n=125) and dizzy older people with significant impairment and at high risk of chronic dizziness with persistent impairment (group B and C, n=125 each). Dizzy older people with significant impairment and a high risk of chronic dizziness will be randomised to group B or C (randomisation will take place at practice level). The validation study consists a low risk usual care group (group A) and a high risk usual care group (group B). The intervention study consists of impaired dizzy patients with a 'high risk' that will receive usual care (group B) or an intervention (group C).

## 4. STUDY POPULATION

### 4.1 Population (base)

This study concerns patients in the primary care setting. Patients will be recruited from the Academic Network of General Practices of the VU University Medical Center (ANH-VUmc) and the General Practitioners Cooperative Twente (Twentse huisartsenonderneming Oost Nederland).

### 4.2 Inclusion criteria

In order to be eligible to participate in this study, a subject must meet all of the following criteria:

- being 65 years or older
- consulted a general practitioner for a new episode of dizziness, defined as recurrent dizziness for at least one month, including a giddy or rotational sensation, loss of balance, faint feeling, light-headedness, instability, or tendency to fall
- current dizziness-related impairment (DHI  $\geq$  30)
- ability to speak, read and write Dutch

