Several members of our research group initiated the study Dizziness In Elderly Patients (DIEP) in collaboration with the Department of General Practice of the Academic Medical Center Amsterdam in order to fill the gap of knowledge about dizziness in older patients. This study resulted in more knowledge of epidemiology, aetiology, and diagnosis of dizziness in older patients in general practice. Furthermore, a large cohort study investigating the prognosis of dizzy older patients in general practice recently identified seven risk factors for chronic dizziness with persistent impairment. These risk factors are (1) onset of dizziness more than six months ago, (2) dizziness provoked by standing still, (3) trouble with walking and/or falling as associated symptom, (4) polypharmacy, (5) absence of diabetes, (6) anxiety and/or depressive disorder, and (7) impaired functional mobility. Three

of these risk factors are amenable to treatment: polypharmacy, anxiety and/or depressive disorder, and impaired functional mobility.

The results of this cohort study, combined with previous findings of DIEP, provide the basis of the present research proposal.

The first objective of the proposed study is to externally validate our previously developed 7-item risk score for chronic dizziness with persistent impairment. Although the discriminative ability of our developed risk score was good (area under the receiver operating characteristic curve [AUC] of 0.80), it is necessary to validate prediction models in new individuals before they can be implemented in guidelines or applied in clinical practice. If our risk score confirms our previous findings, GPs will have an accurate, easy-to-use clinical tool to identify dizzy older patients with a poor functional prognosis.

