### 4.4 Sample size calculation

#### Intervention study

The sample size calculation for our intervention study is based on the difference in 1-year DHI score change between the high-risk intervention group and the high-risk usual care group. We consider a DHI score difference of 12 or more to be a clinically relevant difference. The mean DHI score of patients above 65 consulting their GP because of dizziness is 36.3 with a standard deviation of 19.9. In order to detect a clinically relevant

difference with  $\alpha=0.01$  and  $\beta=0.90$  we used the following formula to calculate the sample size:

$$n = 2(2.58+1.28)^2 \cdot S^2/D^2$$

With  $n$  = number of patients,  $S$  = standard deviation,  $D$  = clinically relevant difference

A group size of  $n=82$  is sufficient  $(2(2.58+1.64)^2 \times 19.92^2/12^2)^{29}$ . However, we need to apply an extra correction since the proposed study is a cluster randomised trial. The correction that needs to be applied by performing an cluster randomised trial can be calculated with the following formula:

$$n = 1+(k-1) \cdot \rho$$

With  $n$  = number of patients,  $k$  = cluster size,  $\rho$  = intra-class correlation (ICC)

Based on secondary analysis of DIEP data we expect a cluster size of 5 patients per practice. An ICC of 0.01 is often used in sample size calculation in primary care research. However, we used an ICC of 0.05 to get a more conservative sample size. The correction factor for performing a cluster randomised trial is 1.2  $(1+(5-1) \cdot 0.05)$ . This means that a groups size of  $n = 99$   $(1.2 \cdot 82)$  is sufficient. Taking into account a loss to follow-up of 20% we need 124 participants in each arm. Thus, a total of 250 patients will be included in the intervention study.

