### 10.1 Primary study parameter(s)

#### I. Validation study

The external validity of our 7-item risk score will be quantified by assessing the reliability, discrimination and calibration of the model. The reliability of the model will be quantified with the Hosmer-Lemeshow goodness-of-fit statistic. We will assess the calibration of the model by plotting the predicted probabilities against the observed frequencies of persistent dizziness-related impairment. We will assess the discriminative ability of the model, i.e. its ability to distinguish dizzy patients with persistent dizziness-related impairment from dizzy patients without persistent dizziness-related impairment, by calculating the receiver operating characteristic curve (AUC). An AUC of 0.5 indicates no discrimination above chance, whereas an AUC of 1.0 indicates perfect discrimination. We will use R statistical software for bootstrapping to adjust for over-optimism in model performance.

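### The 7-item risk score is validated only in patients with baseline DHI of at least 30, but the tool is claimed for dizzy older patients without a DHI limit

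*Protocol*

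**What the plan says.** Section 4.2 makes "current dizziness-related impairment (DHI" of at least 30) an inclusion criterion for every participant. Section 3 describes the validation sample: "The validation study consists a low risk usual care group (group A) and a high risk usual care group (group B"). Both groups are described there as significantly impaired at baseline.

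Section 2 lists the seven predictors, and baseline DHI is not among them. Section 4.4 (Validation study) defines the predicted outcome as DHI of at least 30 at 6 months. It expects this in 60% of patients who start at 30 or above.

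On performance and use, section 1 reports an "area under the receiver operating characteristic curve [AUC] of 0.80" for the original score. It continues that "If our risk score confirms our previous findings", then "GPs will have an accurate, easy-to-use clinical tool to identify dizzy older patients with a poor functional prognosis". The summary and section 11.4 word the aim in the same way, with no DHI limit. Only the new score, planned in section 4.4, is tied to impaired patients.

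Section 10.1 plans the AUC, a calibration plot and a goodness-of-fit test: "The reliability of the model will be quantified with the Hosmer-Lemeshow goodness-of-fit statistic". Bootstrapping is added against over-optimism.

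**The concern.** There are two separate issues.

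1. **Scope.** The claim is wider than the sample. No patient with a baseline DHI below 30 enters the validation, so it gives no information on the score in them. Secondary objective 4 names non-impaired older dizzy patients as a group of their own, so the protocol itself draws the distinction.

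2. **Interpretation.** Suppose the score was built in patients with any DHI. Its predicted risks then average over people who start low and people who start high. Selecting only those who start at 30 or above raises the true risk, and the score can follow that rise only as far as its seven items correlate with baseline DHI. A sound score could then look too low on the calibration plot and in the Hosmer-Lemeshow test. Nothing in section 10.1 would separate that from a faulty score. This bears on primary objective 1.

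**Working it through.** **The plan's own figures (section 4.4).** Expected events: 0.6 × 250 = 150. Predictors at 10 events each: 150 / 10 = 15. Minimum for the 7-item score: 7 × 10 = 70. All three reproduce.

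**Did the earlier cohort include patients below 30?** Section 4.4 says: "The mean DHI score of patients above 65 consulting their GP because of dizziness is 36.3 with a standard deviation of 19.9". The DHI runs from 0 to 100 (section 8.3). If every score lay between 30 and 100 with mean 36.3, the largest possible SD would be √[(36.3 − 30) × (100 − 36.3)] = √(6.3 × 63.7) = 20.03. An SD of 19.9 would then need almost all scores at exactly 30 or exactly 100, which is not credible. With a normal approximation, the share below 30 is Φ[(30 − 36.3)/19.9] = Φ(−0.317) ≈ 0.38. The 60% persistence figure is likewise given for patients at or above 30, that is, for a subset.

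**What would selection do to a correct score?** The documents do not give the correlations needed, so these are assumptions: baseline DHI with the score 0 to 0.5, and baseline DHI with 6-month DHI 0.3 to 0.7. Baseline DHI, score and 6-month DHI were simulated as trivariate normal (200,000 draws). The AUC was fixed at 0.80 in all patients and the event rate at 60% among those starting at 30 or above. The score was calibrated in the whole population and then applied only to baseline DHI of at least 30. Observed risk is 60% throughout. Each cell gives mean predicted risk, observed/expected ratio and AUC in the selected group.

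| Baseline DHI–score correlation | Baseline–6-month correlation 0.3 | 0.5 | 0.7 |
|---|---|---|---|
| 0 | 52.7%; 1.14; 0.81 | 47.4%; 1.27; 0.83 | 42.4%; 1.41; 0.87 |
| 0.2 | 55.9%; 1.07; 0.80 | 50.5%; 1.19; 0.80 | 45.4%; 1.32; 0.82 |
| 0.4 | 58.9%; 1.02; 0.79 | 53.8%; 1.12; 0.78 | 48.4%; 1.24; 0.78 |
| 0.5 | 60.5%; 0.99; 0.79 | 55.2%; 1.09; 0.77 | 50.1%; 1.20; 0.76 |

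The score under-predicts in 11 of 12 settings (ratio 1.02 to 1.41) and is essentially calibrated in one (0.99). The calibration intercept runs from −0.03 to +0.97.

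**Would it show?** The standard error of the observed risk with 250 patients is √(0.6 × 0.4 / 250) = 0.031, about 3 points. Most of the gaps in the table exceed two standard errors, but the smallest do not. The standard error of the AUC with 150 events and 100 non-events is about 0.03, so most of the AUC shifts would be hard to tell from chance.

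For the Hosmer-Lemeshow test, take 10 groups, 200 evaluable patients, score correlation 0.2 to 0.5 and baseline–6-month correlation 0.4 to 0.7. The test then rejects a correct score with probability 0.07 to 0.94. The 200 is 250 less 20%, a loss the protocol states only for the intervention study.

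**The case against.** - **The derivation population is not stated.** The mean of 36.3 and SD of 19.9 are cited to one report of the earlier dizziness study. The score and its AUC are cited to another. The SD bound applies to the first and reaches the score only if the second used the same patients without a DHI restriction. This stands, and it makes the calibration argument conditional.

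- **No formal comparison with 0.80 is planned.** A reader might infer from section 1 that the score passes or fails against 0.80. Section 10.1 sets no such test or threshold; it anchors the AUC only at 0.5 and 1.0. A changed AUC is also not miscalibration, and here it can move either way. This stands.

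- **The restriction is open.** Sections 3 and 4.2 state it, and the word persistent can suggest impairment at baseline. That helps only in part: section 4.4 defines the outcome solely by the 6-month DHI, and the sentences on intended use carry no limit.

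- **Finding such a shift is what external validation is for.** If the published score under-predicts in patients at or above 30, it is miscalibrated for them and users need to know. This stands. It rules out replacing the published intercept before the validation, because that would test an updated model and could hide a real fault.

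- **Detail of calibration reporting often belongs in the analysis plan.** True, but the objective and the intended-use claims are protocol text, and section 10.1 already fixes the measures.

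**Conclusion.** The mismatch in scope is established from the protocol alone and needs no simulation. The validation can speak only for patients with baseline DHI of at least 30, while the tool is offered for dizzy older patients generally.

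The calibration consequence is possible but not shown. It rests on derivation in the unrestricted cohort, which is plausible from the cohort's mean and SD but not stated, and on correlations that the documents do not give. Over the assumed range the effect runs from nil to about 18 points of risk (60% − 42.4% = 17.6).

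A reader might infer that the score is bound to look miscalibrated, or that its AUC must fall. The documents support neither. The low end of the range is harmless, and the AUC may rise as well as fall.

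**What to change.** 1. Limit objective 1 and the intended-use statements in the summary and sections 1 and 11.4 to older patients with dizziness-related impairment (DHI of at least 30).
2. State the baseline DHI range and the event rate of the cohort in which the score was derived. If that cohort was already restricted to 30 or above, one sentence saying so settles the calibration question.
3. Keep the validation of the published score as it is. Beside the Hosmer-Lemeshow statistic, report calibration-in-the-large (the intercept) and the calibration slope.
4. Add, as a supplementary benchmark only, the score's AUC and calibration in the DHI≥30 subset of the derivation data. A score that shows the same shift there points to case mix; one that does badly only in the new sample points to the score.

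The cost is a narrower claim, some wording, and a small re-analysis of data that the group already uses for planning. Enrolment does not change.
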